### Measures

In each assessment session, the parent is invited to participate in a video recording of a 5-min parent–child interaction and asked to complete a self-report questionnaire taking approximately 30 min.

#### Socio-demographic information

We are obtaining information on the parent’s socio-demographic details (age, nationality, educational level, professional occupation, economic condition) and information about pregnancy and post-partum period.

### Outcomes

The primary outcome is the child’s language development. Secondary outcomes are the child’s behaviour, parental mood (anxiety, depression and stress) and parenting.

### Primary outcome

#### The MacArthur-Bates Communicative Development Inventory (CDI)

Parents are asked to complete the short form of the CDI [97], one of the most widely used and recommended measures of language and communication for young children. This provides an assessment of the expressive and receptive vocabulary of 8–36-month infants. Parents identify words that the child is able to understand and those that the child can enunciate from a 100-word checklist. A raw score for expressive and for receptive language is obtained. The Italian version of the CDI [98] has been employed in several cross-cultural studies investigating the linguistic development of young children [99, 100]. The instrument showed adequate validity: high correlations between parent-report scores and child performance on concurrent standardised tests have been reported [101–103].

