### Study design

This is a multicentre, two parallel arms, single blinded randomised controlled superiority trial, with a 1:1 arms allocation ratio. The study followed the SPIRIT reporting guidelines (Supplementary File).

Within each health, educational and maternal-child centres, parent–child dyads are randomly assigned by local staff to either the index group or the control condition based on a randomisation list compiled using random blocks algorithm. The index group receive the DBS intervention immediately, and the control group enter a waiting list and receive the DBS intervention after the final study assessment. The local staff, not involved in the participant treatment and blinded to treatment allocation, collect the baseline data during an interview before randomisation and again after the four group sessions. A follow-up evaluation is to be carried out 6 months after the end of the training.

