### Sample size estimation

The sample size was calculated based on the difference of the number of words between the two study groups (index and control group) at post-test. In the Dowdall meta-analysis, the average effect size for expressive language adjusted for baseline pre-test value was 0.41. Taking this value as the reference to compute the sample size for our study, assuming a *t*-test for independent samples, a two-sided 5% significance level, a sample size of 190 (95 in each groups) will provide a power of at least 80% (PASS 2021).

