### Statistical analysis plan

Descriptive statistics will be performed on socio-demographic and baseline child cognitive-behavioural variables using summary statistics such as mean, standard deviation, median and interquartile range. Comparison of test scores measure, derived as combination of individual score items, at post-test between the two groups will be performed using a linear mixed model accounting for baseline (pre-test) test scores values and a random term to account for recruitment centre effect. Individual items measured on an ordinal scale will be compared using cumulative link models for ordinal measures. Results will be reported as effect estimates and corresponding 95% confidence intervals. All tests will be two-sided and will be evaluated assuming a 5% significance level. This analysis will be performed by an independent statistician, blinded for the treatment allocation. The statistician will report to the Data Monitoring Committee. Data will be analysed based on intention to treat principles. A sensitivity analyses will also be performed, excluding not-adherent participants from the analyses.

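### The primary outcome is a domain with two CDI scores and neither is named as primary, while the sample size rests on expressive language alone

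*Protocol article*

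**What the plan says.** Four places in the Protocol article bear on this.

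- **Outcomes:** "The primary outcome is the child’s language development". This is a domain; no score is named.
- **Primary outcome, CDI:** parents mark, on a 100-word checklist, which words the child understands and which the child says. Then: "A raw score for expressive and for receptive language is obtained". Both scores stand under the primary heading with equal status.
- **Sample size estimation:** "The sample size was calculated based on the difference of the number of words between the two study groups", at post-test. The effect size comes from a meta-analysis in which "the average effect size for expressive language adjusted for baseline pre-test value was 0.41". With "a two-sided 5% significance level" and a t-test, the section arrives at 190 dyads, 95 per arm, for at least 80% power.
- **Statistical analysis plan:** scores are compared at post-test with a linear mixed model that accounts for baseline and centre. "All tests will be two-sided and will be evaluated assuming a 5% significance level". The section does not say which CDI score decides the primary question or how two primary scores would be combined.

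**The concern.** The outcome sections hold two scores, the sample size has an effect for one, and the testing rule treats all tests alike. The reference to a number of words in the sample size section does not settle the matter, because both CDI scores are word counts. Only the expressive effect of 0.41 hints at which was meant.

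This matters because the primary variable decides whether the trial is positive. As the text stands, a significant receptive result beside a null expressive result could be reported as success on the primary outcome, although the documents give no effect size for receptive language. The choice between the scores would also remain open after the results were seen.

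**Working it through.** **Inputs from the Protocol article.** Standardised effect 0.41 (expressive language), two-sided alpha 0.05, 95 per arm, 1:1 allocation, t-test for independent samples, two raw scores under the primary outcome.

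**Input not in the documents.** The correlation r between the two test statistics, which is close to the correlation between the two scores after baseline adjustment. It is treated as an assumption and varied.

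**Step 1: reproduce the plan's figure.** Normal approximation:

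n per arm = 2(1.960 + 0.842)² / 0.41² = 2 × 7.85 / 0.1681 = 93.4, so 94.

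Noncentral t, with noncentrality 0.41 × √(95/2) = 2.83 and 188 degrees of freedom, gives power 0.799 at 94 per arm and 0.803 at 95. The plan's 95 per arm (190 in total) is therefore exact for one test at 5%.

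**Step 2: three readings of the primary outcome.**

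*(a) Expressive score only.* Type I error 5%, power 80.3%. Both stated properties hold.

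*(b) Either score may count.* With no effect on either score, the chance of at least one significant result is

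1 − P(|Z₁| ≤ 1.96 and |Z₂| ≤ 1.96), with (Z₁, Z₂) bivariate normal with correlation r.

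At r = 0 this is 1 − 0.95² = 0.0975. For other values:

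| Assumed r | Type I error |
|---|---|
| 0 | 9.75% |
| 0.3 | 9.5% |
| 0.5 | 9.1% |
| 0.7 | 8.4% |
| 0.8 | 7.8% |
| 0.9 | 7.0% |
| 0.95 | 6.5% |

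*(c) Both scores must be significant.* Type I error is at most 5%. Power cannot exceed that of the expressive test, 80.3%, and reaches it only if the receptive test succeeds whenever the expressive one does. If the receptive effect were also 0.41 (an assumption) and the tests were independent, power would be 0.803² = 0.645, about 64%. Positive correlation would bring it between that value and 80.3%.

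**Step 3: splitting alpha.** If both scores stay primary at 2.5% each, noncentral-t power at 0.41 and 95 per arm is 0.714. To restore 80% takes 115 per arm (power 0.802; 114 gives 0.799), or 230 in total, an increase of 230 − 190 = 40 dyads. This again uses the expressive effect size.

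**The case against.** The strongest defence is that the sample size section already points to words produced at post-test: it sizes on a word count and uses an expressive effect. On that view only a label is missing from the outcome sections. That is fair as to intent and explains why the repair is cheap, but the outcome sections do not say it and nothing in the article rules out the other readings.

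A second defence is that the order of testing and any multiplicity adjustment are commonly left to an analysis plan, and the full one is not shown. This also stands, and the absence of an adjustment method is not the point made here. What remains is a mismatch within the published text: two scores under the primary heading, one effect in the sizing, one flat 5% rule. An unseen plan could resolve it, but the published definition would still not match its own sample size.

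Two stronger readings are tempting and are not supported.

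- A reader might infer that the primary false-positive rate *is* about 8–10%. That needs a rule that either score alone suffices, and no section states one; saying that two raw scores are obtained describes how the instrument is scored. It also needs a correlation no higher than about 0.75. Both scores come from one checklist filled in by one parent, so a higher value is plausible.
- A reader might add the 6-month visit and count four primary tests. The sample size and analysis sections both place the comparison at post-test, and no section makes the 6-month assessment a primary time point.

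**Conclusion.** The concern holds as a mismatch between the primary outcome definition and the sample size. Of the three possible readings, only the expressive-only one keeps both the 5% level and the 80% power, and the outcome sections do not state it.

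The size of the problem is conditional. If either score may count, the primary type I error could rise from 5% to as much as 9.75%, and lies between about 6.5% and 9.75% for assumed correlations from 0.95 down to 0. If both must succeed, there is no inflation, but the stated power has no support because no receptive effect size is given. The figure of 190 is correct for a single expressive endpoint under the plan's own assumptions.

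**What to change.** Name one primary endpoint: the CDI expressive raw score (words produced, out of 100) at post-test, the score to which the 0.41 belongs. Make the receptive score a secondary outcome, for example tested at 5% only if the expressive test is significant. Fixed-sequence testing is one acceptable choice; what matters is that a single score is designated. Then align the Outcomes, Primary outcome and Sample size estimation sections, replacing the reference to a number of words by words produced.

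The cost is about a paragraph of wording, and it should be settled before outcome data are unblinded. The sample of 190, the 5% level and about 80% power are unchanged. The one drawback is that no primary claim can then be made on receptive vocabulary alone. Keeping both scores as primary is possible but dearer: at 2.5% each, power falls to about 71% or the sample grows to about 230, and a both-must-succeed rule would need a justified receptive effect size and a new power calculation.

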### Secondary outcomes

i)Child outcome.

#### Child behaviour

The Achenbach System of Empirically Based Assessment (ASEBA) is being used to assess child behaviour [104] with the Child Behavior Checklist 1½-5 (CBCL), a widely used parent report checklist that measures a broad range of behavioural and emotional problems among young children. Parents complete the questionnaire by providing ratings to descriptive statements (0 = not true, 1 = somewhat or sometimes true, 2 = very true or often true). For the current study, the questionnaire comprises 27 items that provide an index of Emotionally Reactive, Attention Problems, Affective Problems and Attention Deficit/Hyperactivity Problems. The CBCL’s scales demonstrated good instrument quality and validity and showed good psychometric properties with regard to consistency, reliability and cross-informant agreement [105].ii)Parental outcomes.

#### Anxiety and depression

To assess parental mood, the Hospital Anxiety and Depression Scale (HADS) is being used [106]. This is a 14-item self-report questionnaire which aims to identify the presence of anxious and depressive symptoms. Each item is rated on a 4-point Likert scale reflecting severity. The HADS is completed on the basis of the emotional state felt over the previous week. Although it was initially developed for patients in hospital settings, several studies have shown that it is appropriate in a wide range of setting, including within the general population [107]. The validation of the original version of this psychometric scale was followed by translations into various languages, including Italian [108].

#### Parenting stress

The short form of the Parenting Stress Index (PSI-SF) [109] is being used. This measure is commonly used to assess parenting stress both in clinical and research contexts. For the current study, we only administer one subscale of the PSI-SF, namely Parent–Child Dysfunctional Interaction (P-CDI). This consists of 12 items rated from 1 (strongly disagree) to 5 (strongly agree) assessing the extent to which parents feel satisfied with their child and their interactions with them.

#### Parenting

The secondary outcome is parenting which is assessed on all three data collection occasions by direct observation. Parents are asked to share the same text-light book with their child (‘Yes’ by Jez Alborourgh) in the way they would at home. The interactions are filmed. Five minutes of interaction are rated on measures of parental behaviour and parent–child interaction [48]. The measures concern dimensions of book-sharing that the intervention is designed to enhance, and they therefore provide an objective measure of how well parents had implemented the strategies covered in the training programme. Videos and transcripts are scored by trained researchers blind to group and child outcome. Random samples will be scored by independent trained assessors to establish interrater reliability. The principal dimension of parenting assessed is sensitivity*.* This concerns parental appropriate and warm responsiveness to the child [48, 49]. Key aspects include the parent’s awareness of the child’s focus of interest (e.g. gaze direction, pointing, efforts to turn the page) and their communication, as well as the extent to which parental responses to these behaviours were supportive and well timed. The level of sensitivity is rated from the videos on a 5-point scale.

Reciprocity is also rated from these videos. This concerns shared affect (e.g. smiles, expressions of surprise, concern) and joint attention to the book (e.g. gazing and pointing together at the same part of the page), vocal exchanges and gestural turn taking (e.g. stroking motions on depicted book characters) and mutual gaze [48, 49], and was rated from the videos (score = rating on 5-point scale).

### Statistical analysis plan

Descriptive statistics will be performed on socio-demographic and baseline child cognitive-behavioural variables using summary statistics such as mean, standard deviation, median and interquartile range. Comparison of test scores measure, derived as combination of individual score items, at post-test between the two groups will be performed using a linear mixed model accounting for baseline (pre-test) test scores values and a random term to account for recruitment centre effect. Individual items measured on an ordinal scale will be compared using cumulative link models for ordinal measures. Results will be reported as effect estimates and corresponding 95% confidence intervals. All tests will be two-sided and will be evaluated assuming a 5% significance level. This analysis will be performed by an independent statistician, blinded for the treatment allocation. The statistician will report to the Data Monitoring Committee. Data will be analysed based on intention to treat principles. A sensitivity analyses will also be performed, excluding not-adherent participants from the analyses.

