The sessions are conducted with groups of up to six parents, during which children are cared for in an adjoining play space by centre staff. In each session, the facilitator presents parents with different ways to share the book with their children, according to a defined programme. At the beginning of the training course, the trained facilitator promotes discussion among the parents and the sharing of their personal experiences within the group in order to facilitate a collective commitment to the programme. This sense of corporate endeavour is maintained throughout the programme by group discussion of progress. At the end of each group session there is a brief period of one-to-one interaction between the facilitator and each parent together with their child, who are given a book to take home with them, and they are given support and encouragement in applying the acquired dialogic book-sharing techniques with their child using this book. After being exposed to new techniques of book-sharing during each group session, parents are advised to apply these techniques autonomously during the following week in their daily life with their children. After the four sessions of the intervention, parents will be encouraged to continue to apply the full set of techniques with their child over the next 6 months.

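### DBS is taught in small groups in one arm only, but the model has only a centre term, and the 190 has no margin if outcomes correlate within teaching groups

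*Protocol article*

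**What the plan says.** **Delivery.** Under *Training programme for healthcare professionals*: "The sessions are conducted with groups of up to six parents". A facilitator leads each session, and shared group influence is intended: "This sense of corporate endeavour is maintained throughout the programme by group discussion of progress".

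**Design.** Under *Study design*, dyads are randomised individually within centre, "with a 1:1 arms allocation ratio", and "the control group enter a waiting list and receive the DBS intervention after the final study assessment". Grouping before the outcome therefore exists in the DBS arm only.

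**Analysis.** Under *Statistical analysis plan*, scores at post-test are compared "using a linear mixed model accounting for baseline (pre-test) test scores values and a random term to account for recruitment centre effect". No term for teaching group, or for centre by arm, is named. The statistician is to be blinded to allocation, and the analysis follows intention to treat.

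**Sample size.** Under *Sample size estimation*, "the average effect size for expressive language adjusted for baseline pre-test value was 0.41". The test is an independent-samples t, described as "test for independent samples, a two-sided 5% significance level", and the result is that "a sample size of 190 (95 in each groups) will provide a power of at least 80% (PASS 2021". No intraclass correlation or design effect enters.

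**The concern.** Parents who share a facilitator and discuss their progress together may end up with more similar outcomes than parents in different groups. Because randomisation is within centre, a centre intercept is shared by DBS and control dyads and drops out of the within-centre arm contrast. A teaching-group effect touches only DBS dyads. It stays in the contrast but is not represented in the model's standard error.

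Two things are at stake. Confidence intervals would be too narrow and the error rate above 5% for every test score analysed this way, secondary outcomes included. The stated power also rests on independent dyads, with nothing in hand if that assumption fails.

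**Working it through.** **Inputs from the protocol article.** Effect size 0.41, two-sided 5%, 95 per arm (*Sample size estimation*); groups of up to six (*Training programme for healthcare professionals*); 12 centres (*Objectives*; Table 1).

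**Assumptions, because the document gives no figure.** ICC within a DBS teaching group of 0.02, 0.05 or 0.10. Group size m of 4 or 6. Six is the ceiling. An even spread gives 95/12 ≈ 8 DBS dyads per centre, which suggests two groups of about four.

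**1. The plan's own figure.** The normal formula gives 2(1.96 + 0.84)²/0.41² ≈ 93.3, so 94 per arm. The noncentral t gives 79.9% power at 94 per arm and 80.3% at 95. The 190 is reproduced and is the smallest number that meets the claim.

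**2. Effect of grouping in one arm.**
- Design effect in the DBS arm: DE = 1 + (m − 1) × ICC. In the control arm it is 1.
- True SE / model SE = √[(DE + 1)/2].
- Actual error of the nominal 5% test = 2[1 − Φ(1.96 / SE ratio)].
- Power of a test using the correct SE: noncentral t with 188 degrees of freedom and noncentrality 0.41/√[(DE + 1)/95].

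Example, m = 6, ICC 0.05: DE = 1 + 5 × 0.05 = 1.25; SE ratio = √(2.25/2) = 1.061; error = 2[1 − Φ(1.848)] ≈ 6.5%; noncentrality = 0.41/√(2.25/95) ≈ 2.66; power 75.5%.

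| m | ICC | DE | SE ratio | Error, planned test | Power, valid test |
|---|---|---|---|---|---|
| 4 | 0.02 | 1.06 | 1.015 | 5.3% | 79.1% |
| 4 | 0.05 | 1.15 | 1.037 | 5.9% | 77.4% |
| 4 | 0.10 | 1.30 | 1.072 | 6.8% | 74.6% |
| 6 | 0.02 | 1.10 | 1.025 | 5.6% | 78.3% |
| 6 | 0.05 | 1.25 | 1.061 | 6.5% | 75.5% |
| 6 | 0.10 | 1.50 | 1.118 | 8.0% | 71.0% |

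The last two columns describe different analyses. The error is that of the planned test; the power is that of a test whose standard error allows for the groups. The planned test would still reject about as often as advertised at d = 0.41 (79 to 80% in the simulation below, at ICC 0.05 and 0.10), but only because its error rate is too high. The 188 degrees of freedom are generous, since a model with a group term would have fewer.

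**3. Does the centre term absorb it?** Simulation with 12 centres of 16 dyads, DBS groups of 4 + 4 or 6 + 2 per centre, and centre adjusted for. Repeated runs gave an error rate of about 5.1 to 5.4% at ICC 0, 5.8 to 6.8% at ICC 0.05 and 7.0 to 7.8% at ICC 0.10. It does not.

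**4. Scale of the 0.41.** If 0.41 is a baseline-adjusted difference divided by the raw SD, adjustment multiplies the SE by √(1 − r²), where r is the baseline correlation. At r = 0.5 the factor is 0.866. Power at 95 per arm is then 90% without grouping and 86% at ICC 0.05 with groups of six, without loss. If 0.41 is already scaled by the adjusted SD, no such gain remains and the table applies.

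**The case against.** A reader might infer that the intervals are certainly too narrow and that 80% power is certainly not delivered. The documents do not support that. They give no ICC, and at 0.02 without loss the power shortfall is only one to two points. Six is the maximum group size, and groups of about four soften every figure. *Sample size estimation* does not say which SD scales the 0.41, and on the raw-SD reading power may stay above 80%. This part of the objection stands, and it is why the point is conditional.

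It does not rescue the standard error. A gain from baseline adjustment raises power, but it leaves the group effect out of the model, so any positive ICC still makes the interval too narrow.

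It would also be tempting to count missing allowance for dropout as a fault. The powered comparison is at post-test, after a four-week course, so losses by six months do not bear on it. The article does not say whether 190 means enrolled or analysed, and an attrition allowance is a detail it may leave to the full protocol. What remains is only that the calculation has no slack.

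Objections to the remedy are fair too. Group codes in one arm can reveal allocation to a blinded statistician. Some DBS dyads may never attend a group. With roughly 95/6 ≈ 16 to 95/4 ≈ 24 groups, the group variance will be imprecisely estimated. The fix has to deal with each of these.

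**Conclusion.** The point holds as a conditional one. The stated model omits a source of correlation that the delivery of the intervention makes plausible, and the centre term does not stand in for it. For an ICC of 0.02 to 0.10, the error rate by formula is 5.3 to 6.8% with groups of four and 5.6 to 8.0% with groups of six. That is a modest excess, but it comes from a stated analysis rule and is easily avoided.

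The claim of at least 80% power is correct for 95 independent, analysed dyads per arm and for nothing less. Under a valid test it falls to between 79.1% and 71.0% across the cases shown, if 0.41 already contains the gain from baseline adjustment. If it does not, power may be adequate. The ICC, the group size and the scale of the 0.41 are assumptions that only the sponsor can settle.

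**What to change.** **Analysis.**
- Record the teaching-group identifier for each DBS dyad.
- Keep the baseline score and random centre term, and add a random teaching-group effect for the DBS arm only. Each control dyad, and each DBS dyad never placed in a group, forms its own cluster, so that intention to treat is preserved.
- Use Satterthwaite or Kenward-Roger degrees of freedom.
- Prespecify a simpler fallback in case the group variance cannot be estimated.

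**Sample size text.** State that 80.3% applies to 95 analysed, independent dyads per arm. Say which SD scales the 0.41. Give power under the model to be fitted for an assumed ICC, group size and baseline correlation.

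**Blinding.** Because the cluster structure can reveal the arm, prespecify and lock the analysis code before the identifiers reach the blinded statistician.

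**Cost.** One recorded variable, slightly wider intervals, a less favourable stated power and the blinding step above. No extra enrolment is needed. The change should be made before the outcome data are analysed, since adding the term afterwards would be open to challenge.

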## Introduction

### Background

In the first years of life, non-verbal communication and language skills develop rapidly, and children learn that their caregivers’ behaviour contains important information about the world [1, 2]. One of the first aspects of early parent–child interactions that help child development is the emergence of joint visual attention between an adult and an infant about a common focus, for example, an object. Another critical aspect of early development that underpins shared understanding and communication is the acquisition of language [3]. Language is a skill that influences other domains, such as social and cognitive development, and requires social interaction [4–6]: language learning relies on children’s desire to imitate [7] and on their appreciation of their caregivers’ communicative intentions [8]. Young children’s learning occurs mainly in a dyadic context of an interaction with a knowledgeable caregiver: from this perspective, good dialogic parent–child communication that involves reading to the child at an early age is highly effective in promoting communication and language development [9–11]. Research on parent–child shared-reading interventions in early childhood [12] has highlighted the benefits for early language acquisition [13] and for accelerating language development [14]. Benefits for child’s linguistic development occur following regular and dialogic reading [15], results confirmed by meta-analyses [16, 17]. Language learning through situation-specific practices, such as reading, in which parents label items more frequently than during other activities such as playtime or mealtime, provides children with particularly consistent and informative linguistic feedback [18, 19]. By reading books to children, caregivers support a wide range of skills. These include reinforcing the acquisition of new words and concepts [20, 21], promoting the child’s literacy skills [22] and providing a ‘lexical reservoir’ that widens vocabulary [23]. In addition, the activity of parent–child shared reading has a significant impact on the development of preschoolers’ abstract language [24], syntactic quality, complexity of sentence construction [25], literal and inferential language [26], listening comprehension, phonemic awareness [27] and receptive and expressive vocabulary [28].

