### Selection criteria

#### Inclusion criteria

Mothers and fathers who are able to speak and read ItalianChildren aged 14–20 months at the time of the baseline assessment

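### The stated primary model adjusts the raw CDI word count for baseline score and centre but not for the child's age, which may give up some precision at no saving

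*Protocol article*

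**What the plan says.** All references are to the protocol article.

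- **Statistical analysis plan:** post-test scores are compared between arms with a linear mixed model "accounting for baseline (pre-test) test scores values and a random term to account for recruitment centre effect". No other adjustment term is named.
- **Primary outcome (CDI):** parents mark words on a 100-word checklist. "A raw score for expressive and for receptive language is obtained". No conversion to age norms is described.
- **Inclusion criteria:** children are "aged 14–20 months at the time of the baseline assessment".
- **Background:** in the first years of life "non-verbal communication and language skills develop rapidly".
- **Study design:** allocation is by random blocks within centre, with no age stratum described. Data are collected before randomisation and "again after the four group sessions".
- **Socio-demographic information:** age is listed only among the parent's details. That the child's age is known follows from the eligibility criterion, not from a stated data item.
- **Sample size estimation:** the calculation uses a baseline-adjusted effect size of 0.41 for expressive language and makes no use of age.

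**The concern.** A raw vocabulary count rises with age, and the eligible range covers six months of a period that the protocol itself describes as one of rapid development. The baseline count carries some of that age information but need not carry all of it, since two children with the same count can differ in age and in how fast they are progressing. Whatever age-related variation remains after adjusting for the baseline count stays in the residual and widens the confidence interval for the treatment effect. Allocation is not described as balanced on age, so a chance age difference between arms would be corrected only as far as the baseline count reflects it. What is at stake is precision, in a design whose calculated power is barely above its target.

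**Working it through.** **1. Reproduce the plan's figure.** Inputs from Sample size estimation: standardised effect 0.41, "a two-sided 5% significance level", "a sample size of 190 (95 in each groups"), and the claim that this "will provide a power of at least 80"%.

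- Normal approximation: n per arm = 2(1.960 + 0.842)² / 0.41² = 93.4, rounded up to 94 (188 in total).
- Exact two-sample t-test: 94.35 per arm, rounded up to 95 (190 in total), with power 80.3%.

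The stated 190 reproduces, without age in the model.

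**2. Chance age imbalance.** Assumption: ages are spread evenly over 14–20 months.

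- SD of age = √(6²/12) = 1.73 months.
- SD of the difference in mean age = 1.73 × √(2/95) = 0.25 months.
- 95% range = ±1.96 × 0.25, about ±0.49 months.

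**3. Effect of adding age.** Let r be the partial correlation of age with the post-test score given the baseline score. Adding age multiplies the residual variance by (1 − r²), so the standardised effect becomes 0.41/√(1 − r²). The protocol gives no value for r, so every non-zero row is an assumption. Like the plan's own calculation, this treats 0.41 as the effect relative to the SD left after baseline adjustment. It makes no allowance for dropout or centre.

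| Assumed r | Residual variance retained | Standardised effect | Fall in standard error | Power, 95 per arm (exact t) |
|---|---|---|---|---|
| 0 | 100% | 0.410 | 0% | 80.3% |
| 0.1 | 99% | 0.412 | 0.5% | 80.7% |
| 0.2 | 96% | 0.418 | 2.0% | 81.8% |
| 0.3 | 91% | 0.430 | 4.6% | 83.8% |
| 0.4 | 84% | 0.447 | 8.3% | 86.6% |

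**4. Why r can be small.** What counts is the partial correlation, and the baseline score comes from the same checklist some weeks earlier. With marginal correlations a = r(age, post), b = r(age, baseline) and c = r(baseline, post),

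r = (a − bc) / √[(1 − b²)(1 − c²)].

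Three illustrations, all with assumed values:

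- a = 0.4, b = 0.4, c = 0.8: r = 0.08 / √(0.84 × 0.36) = 0.145, or 2.1% less residual variance.
- a = 0.4, b = 0.5, c = 0.8: numerator 0.4 − 0.40 = 0, so r = 0 and nothing is gained.
- a = 0.5, b = 0.4, c = 0.7: r = 0.22 / √(0.84 × 0.51) = 0.336, or 11.3% less residual variance.

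Plausible-looking inputs therefore run from no gain to a moderate one, and the protocol cannot narrow that range.

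**The case against.** The strongest objection is one of scope. A journal article condenses the plan, a full covariate list commonly sits in a separate analysis plan, and one sentence naming two terms does not rule out a third. That stands to this extent: the article contradicts nothing, and if a fuller plan already includes age, the sponsor need only confirm it. It does not dispose of the point, because the section is the article's own statistical analysis plan and states its adjustment terms. Proposing a better version of that stated model is fair comment.

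A second objection is that baseline adjustment is already the main precision step and that the power target is met without age. Both statements are correct, and they limit the point to a possible small gain.

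A reader might go further and infer one of the following, none of which the article supports:

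- **That the treatment estimate is biased or the trial underpowered.** Randomisation protects the comparison in expectation, and 190 reproduces.
- **That the precision lost is known.** No correlation of age with score, growth curve or residual variance is given.
- **That the loss is greater at 6 months, or extends to the CBCL.** The stated model concerns post-test only, and the remark on rapid development concerns communication and language, not behaviour.
- **That visit timing differs between arms because controls attend no sessions.** This is a separate question, which an age-at-baseline covariate would not answer. The article states no such difference, and its schedule figure is not shown.

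**Conclusion.** The point holds as a missed, nearly costless efficiency. The stated model for the raw CDI count omits a baseline variable that is known for every child and is likely to be related to the outcome. If the partial correlation given baseline is 0.2 or less, the gain is at most about 1.5 power points (80.3% to 81.8%). At 0.3 it is about 3.5 points (to 83.8%), and it may be near nil. These power figures rest on the assumed partial correlation and on the plan's 0.41, which refers to expressive language. The imbalance figure rests on evenly spread ages. The case for including age is its negligible cost and the value of settling the choice in advance, so that it is not made after an imbalance has been seen.

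**What to change.** In the Statistical analysis plan, name the child's age in months at baseline as a fixed covariate, alongside the baseline score and the random centre term, in the linear mixed model for the CDI scores at post-test. Fix this before the outcome data are analysed. State that the gain in precision is expected to be small and that the sample size does not rely on it. If a fuller analysis plan already includes age, a sentence confirming this is enough.

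The cost is one sentence in the plan and one degree of freedom. No new measurement is needed, because age has to be established to apply the inclusion criterion; it only has to be carried into the analysis dataset.
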